## Abstract

**Introduction:**

Inflammatory bowel disease (IBD), including ulcerative colitis and Crohn’s disease, can be challenging to diagnose, and treatment outcomes are difficult to predict. In the NORDTREAT cohort study, a Nordic prospective multicentre study, we aim to identify novel molecular biomarkers of diagnostic value by assessing the diagnostic test accuracy (cross-sectionally), as well as the prognostic utility when used as prognostic markers in the long-term (cohort study). In the diagnostic test accuracy study, the primary outcome is a successful diagnosis using one or more novel index tests at baseline compared with the ECCO criteria as the reference standard. The composite outcome of the prognostic utility study is ‘severe IBD’ within 52 weeks from inclusion, defined as one or more of the following three events: IBD-related surgery, IBD-related hospitalisation or IBD-related death.

**Methods and analysis:**

We aim to recruit 800 patients referred on suspicion of IBD to this longitudinal observational study, a collaboration between 11 inclusion sites in Denmark, Iceland, Norway and Sweden. Inclusion will occur from February 2022 until December 2023 with screening and baseline visits for all participants and three outcome visits at weeks 12, 26 and 52 after baseline for IBD-diagnosed patients. Biological material (blood, faeces, biopsies, urine and hair), clinical data and lifestyle information will be collected during these scheduled visits.

**Ethics and dissemination:**

This study will explore novel biomarkers to improve diagnostic accuracy and prediction of disease progression, thereby improving medical therapy and the quality of life for patients with IBD.

The study is approved by the Ethics Committee (DK: S-20200051, v1.4, 16.10.2021; IS: VSNb2021070006/03.01, NO: 193064; SE: DNR 2021-05090) and the Danish Data Protecting Agency (20/54594). Results will be disseminated through peer-reviewed journals, patient associations and presentations at international conferences.

**Clinical trial registration number:**

NCT05414578; Pre-results.

STRENGTHS AND LIMITATIONS OF THIS STUDYAll participants included on suspicion of inflammatory bowel disease and treatment naïve.Strong international collaboration and extensive inclusion area with 11 sites in four Nordic countries.Prospective, longitudinal study design with rigorously collected biological material and data on disease activity and lifestyle.Patient heterogeneity (four countries).Ascertainment bias; as some patients with severe disease course may not be eligible for inclusion if acute treatment is initiated.

## Introduction

Inflammatory bowel disease (IBD), primarily ulcerative colitis (UC) and Crohn’s disease (CD) are idiopathic disorders characterised by chronic gastrointestinal inflammation and relapsing symptoms like diarrhoea, abdominal pain and fatigue. A large proportion of the patients experience severe disease manifestations like bowel obstruction, fistulising disease, liver disease and colorectal cancer. Additionally, extraintestinal manifestations occur in 15%–40%.^1^ Consequently, hospitalisations, surgical interventions, recurring sick leave and life-long medication severely impact the lives of patients and families. Even though the incidence of IBD appears to have reached a plateau in most Western European countries, it is rapidly increasing in many newly industrialised countries.^2^ The prevalence of IBD has increased substantially in the last three decades, exceeding 0.5% in many European countries.^2–4^ An estimated 1.3 million people in Europe suffer from IBD, imposing a substantial health, social and economic burden.^1^ There is a need to improve the management of IBD.

Diagnosis of IBD can be cumbersome.^5–7^ Furthermore, IBD is a heterogeneous disease and its course differs substantially between patients. The lack of vigorous biomarkers for individual disease characterisation potentially leads to delayed diagnosis, organ damage, worsened outcome, increased mortality and an ever-increasing disease burden.^8^ Personalised medicine (PM) could be a suitable strategy for optimising both diagnostics and treatment of IBD.^9^ The vision of the International Consortium for Personalised Medicine (ICPerMed) describes ‘an approach to medicine that integrates an individual’s characteristics for early disease diagnosis, prognosis, optimal choice of treatment, accurate disease risk estimation, and targeted prevention’.^10^ In gastrointestinal diseases, PM is based on advancements in biomarker detection in a variety of omics-platforms, including genomics, transcriptomics, microbiomics, proteomics and metabolomics, as well as body imaging methods, for example, CT scans and MRI scans. Recent advances led to the identification of several potential biomarkers for diagnosis and treatment response in IBD.^11–17^ However, they are not in use in clinical practice. Even though early diagnosis and efficient treatment strategies for IBD are cornerstones for reducing irreversible organ damage, identifying biomarkers that can efficiently support clinical decision-making is still warranted.

This protocol article introduces a prospective clinical study that aims to identify novel diagnostic biomarkers for more accurate early diagnosis of IBD and assess the utility of novel prognostic biomarkers in clinical outcomes with various disease manifestations. Notably, the study evaluates biomarkers in a relevant clinical setting, that is, among patients referred to the hospital on suspicion of IBD and diagnosed according to the ECCO criteria.^5^

### Aims

This study aims, on the one hand, to improve accuracy in diagnosing IBD in the form of a *diagnostic test accuracy study*. The main hypothesis is that biochemical markers can differentiate individuals referred to a gastroenterology department with suspected IBD into individuals with (IBD) and without (non-IBD) diagnosis. The primary aim is to identify molecular biomarkers (eg, from blood and stools) for discriminating between individuals diagnosed with IBD (CD, UC and unclassified inflammatory bowel disease (IBD-U)) and non-IBD. Secondary aims include investigating whether clinical, genetic, microbiome and lifestyle information and combinations thereof (eg, gene-environment interaction analyses) are associated with IBD diagnosis.

On the other hand, the main hypothesis of the *prognostic utility study* is that prognostic factors can distinguish different pathways of disease progression. The primary aim of this study is to identify prognostic biomarkers that can define different IBD disease courses. The secondary aims are to evaluate whether including information on clinical and lifestyle factors and combinations thereof can improve prognostic value.

## Methods and analyses

### Design

The NORDTREAT cohort study is a Nordic multicentre collaboration on diagnostic factors and prognostic factors of IBD among patients referred to the hospital with suspected IBD. All referred patients will be carefully evaluated to ensure that patients with suspected IBD are invited to participate in the study at their first clinic visit. Informed consent will be obtained at the screening visit (week −4). After study material collection (ie, blood, stool, biopsies, hair, urine, questionnaires and patient-reported outcome measures (PROMs)) and diagnostic evaluation, IBD diagnosis will be established or rejected at the baseline visit (week 0). IBD patients will be followed until week 52 with three additional visits (weeks 12, 26 and 52), whereas non-IBD patients will complete questionnaires at baseline visit and week 52 (figure 1).

**Figure 1 F1:**
[figure not shown]
Schedule for patients with a suspected IBD diagnosis.

The prospective study consists of a cross-sectional part with focus on diagnosis and a longitudinal cohort study (52 weeks) with focus on prognosis (ie, a prognostic utility study). The inclusion of patients into the NORDTREAT cohort study will be reported as a flowchart (figure 2).

**Figure 2 F2:**
[figure not shown]
Flowchart for patients assessed eligible for inclusion in the NORDTREAT cohort study.

The objective of the *diagnostic test accuracy study* is to determine the sensitivity and specificity of biomarkers of interest (baseline measurements, see Biomarkers section) to diagnose IBD when applying the ECCO diagnostic criteria as the reference standard.^5^

The objective of the *prognostic utility study* is to examine whether the biomarkers of interest predict severe disease outcomes in patients with IBD. Severe IBD is defined as those experiencing IBD-related surgery, IBD-related hospitalisation (except planned procedures) or IBD-related death within 52 weeks of inclusion.

### Setting

This Nordic multicentre study is a collaboration between gastroenterology departments in 11 Nordic hospitals (online supplemental appendix 1). The study enrolment will occur between 7 February 2022 and 31 December 2023. The first patient’s first visit was conducted in Oslo University Hospital in February 2022, and the first patient’s last visit was in February 2023. All inclusion sites will conduct their last patient’s first visit and last patient’s last visit in December 2023 and December 2024, respectively.

10.1136/bmjopen-2023-083144.supp1Supplementary data

### Patient characteristics and eligibility criteria

Inclusion criteria: patients≥18 years of age referred to a gastroenterology department with suspected IBD who give written informed consent to participate in the study. Exclusion criteria: patients with a previous diagnosis of CD, UC or IBD-U or patients unable to provide informed consent or comply with protocol requirements, for example, due to recreational drug or alcohol misuse.

The clinical data and lifestyle information collected for the study will be presented in tabular form (see table 1) and include the following.

### Clinical interview

**Table 1 T1:** Overview of clinical and lifestyle information collected according to visits (weeks after diagnosis)

	IBD				non-IBD	
Week	−4/0	12	26	52	−4/0	52
Clinical information						
Clinical interview and examination	x	x		x	x	
Vital signs	x	x	x	x	x	
Endoscopy	x			x	x	
Medical records	x	x		x	x	
Montreal classification	x			x		
Lifestyle information, disease activity index and PROMs						
SF36	x	x	x	x		
IBDQ	x	x	x	x		
EQ-5D-5L	x	x	x	x		
IBD-F	x	x	x	x	x	x
HBI (CD only)	x	x	x	x		
Partial Mayo score (UC only)	x	x	x	x		
ROME IV	x	x	x	x	x	x
Diet	x			x	x	x

CD, Crohn's disease ; EQ-5D-5L, EuroQol 5 Dimension 5 Level; HBI, Harvey-Bradshaw Index; IBD, inflammatory bowel disease; IBD-F, Inflammatory Bowel Disease Fatigue (part 1); IBDQ, Inflammatory Bowel Disease Questionnaire; PROMs, patient-reported outcome measures; SF36, Short Form 36; UC, ulcerative colitis .

Demographics (sex, age, marital status, educational level, occupational status and smoking), disease history (previous disease including debut of gastrointestinal symptoms) and surgery (abdominal and perianal), occurrence of intestinal complications (defined as strictures and fistulas), occurrence of perianal disease, extraintestinal manifestations, medication (past and present), family history (of IBD and colorectal cancer) and at the week 52 visit: relapses and surgery (abdominal and perianal) are recorded.

### Clinical examination

Includes a perianal examination of study subjects with perianal CD (accounting for the number of draining and non-draining perianal fistula).

### Vital signs

Include measurement of height, weight, heart rate, blood pressure, and temperature.

### Endoscopy

Standardised scoring systems will record macroscopic findings from the ileocolonoscopy: for patients with UC, the Endoscopic Mayo Score per segment is applied, that is, ascending, transverse, descending, sigmoid colon and rectum.^18^ For patients with CD, the Simple Endoscopic Score for Crohn’s Disease (SES-CD) per segment is applied, that is, terminal ileum, ascending, transverse, left colon and rectum.^19^ Patients diagnosed with IBD-U at baseline will be assessed with the Endoscopic Mayo Score per segment and the SES-CD per segment. The endoscopy is recorded on video (approximately 20 s per segment). Furthermore, standard routine biopsies from the ileum, ascending, transverse, descending colon, and rectum will be obtained.

### Medical records

Routine clinical information, clinical findings and procedures (endoscopic and surgical), test results (ie, histology, radiology (including small bowel MRI, capsule endoscopy, CT scan and ultrasonography), microbiology and biochemistry), diagnosis, treatment and complications including hospitalisations will be retrieved from the medical records.

### Montreal classification

Based on results from the routine examinations, the study subjects will be classified according to the internationally accepted IBD classification system, the Montreal Classification.^20^

### Lifestyle information, Disease Activity Index, disease questionnaires and PROMs

Participants will complete validated questionnaires (on paper or electronically) on disease activity, quality of life, including *EQ-5D-5L*
21 (measure of, eg, mobility, personal care, usual activities, pain/discomfort and anxiety/depression), *SF-36*
22 (including perception of health, limitations in daily and social activities, general mental health (psychological distress and well-being), and vitality (energy and fatigue) within the last 4 weeks), *IBDQ*
23 24 (disease impact on patients daily functioning and quality of life, eg, abdominal pain, sleep, incontinence, ability to work and conduct social activities within the last 2 weeks), *IBD-F*
25 (disease-specific questionnaire comprising five questions about the severity of fatigue (part 1) and *ROME IV*
26 (The Rome IV Diagnostic Questionnaire for Functional Gastrointestinal Disorders in Adults). The electronic case report form (eCRF) platform Viedoc (Viedoc Technologies, Uppsala Sweden) is applied, and in Denmark REDCap (Vanderbilt University, Nashville, TN, USA) is used for diet questionnaires.

Before each visit, patients with IBD will register clinical disease activity, Harvey-Bradshaw Index (*HBI*)^27 28^ (diary for patients with CD including two clinical parameters: abdominal pain and number of liquid or soft stools), or *Partial Mayo Score* (diary for patients with UC or IBD-U including the two non-invasive components of the full Mayo Score (stool frequency and rectal bleeding)). All participants will perform diet questionnaires at baseline and week 52.^29^

### Biological material

Blood, biopsies, faeces, hair and urine will be collected at the scheduled visits (table 2).

At baseline, all study subjects have blood samples (whole blood (4 mL), plasma (10 mL), serum (20 mL) and Paxgene blood RNA system (2,5 mL)) and biopsies collected (eight biopsies from predefined locations collected in Allprotect reagent and six biopsies from predefined locations snap frozen in liquid nitrogen or FlashFREEZE (Milestone Medical, product no. 100 780 from Axlab A/S, DK), ensuring a standardised freezing procedure at −80°C). Furthermore, the faecal samples collected at the patient’s home will consist of: one stool collection tube with RNALater, DNA stabiliser and a dry sample, respectively. Additionally, a tuft of hair and urine (8mL) will be collected.

**Table 2 T2:** Overview of the biological material collected in the study

Biological material	Specifications	Baseline	Week 12	Week 26	Week 52
		IBD and non-IBD	IBD	IBD	IBD
Blood	Whole blood (EDTA-K2)	x			
	Plasma (EDTA-K2)	x	x	x	x
	Serum	x	x	x	x
	Paxgene	x			x
Biopsies	Allprotect reagent	x			x
	Snap frozen	x			x
Faecal samples	DNA stabiliser	x	x	x	x
	Dry	x	x	x	x
	RNALater	x	x	x	x
Hair	10–20 mg	x			x
Urine	Spot urine	x			x

IBD, inflammatory bowel disease.

Blood samples will not be collected on the day of the ileocolonoscopy, and faecal samples will not be collected during the colonic cleansing to minimise any potential influence from the standard cleansing procedure conducted before an endoscopy.

On follow-up visits at week 12 and week 26, all patients diagnosed with IBD will have blood samples (plasma (10 mL) and serum (20 mL)) and faecal samples (one stool collection tube with RNALater, DNA stabiliser and a dry sample, respectively) collected. At the week 52 visit for IBD patients, biological material similar to baseline will be collected (except for whole blood). The biological material will be stored at local facilities according to national procedures, and accordingly available for future research projects on approval of the NORDTREAT executive committee. Standard operating procedures with detailed information can be found in online supplemental
appendix
2.

10.1136/bmjopen-2023-083144.supp2Supplementary data

### Primary endpoint(s)

The primary endpoint for the cross-sectional *diagnostic test accuracy study* is diagnosis according to the reference standard from ECCO criteria,^5^ that is, IBD (including CD, UC, IBD-U) or non-IBD (patients not diagnosed with IBD) at referral.

The primary endpoint for the longitudinal *prognostic utility study* is a composite outcome measure. We will include multiple (three mutually associated) endpoint components combined as a Boolean function; this will be our primary outcome measure derived from randomised trials while also anticipating that the approach will be associated with increased statistical efficiency (eg, power). The composite outcome consists of the proportion of patients who experience severe IBD over 52 weeks after inclusion, defined as either IBD-related surgery, IBD-related hospitalisation (except planned procedures) or IBD-related death.

### Key secondary endpoints in the prognostic utility study

Major secondary outcomes assessed and analysed 52 weeks from baseline will include IBD-related surgery (number (no.) in %), IBD-related hospitalisation (no., %), IBD-related deaths (no., %) as well as non-corticosteroid-free (local acting systemic administered (budesonide) and systemic steroids (prednisolone)) clinical remission at week 12.^30^ Clinical remission in CD is defined as patient-reported outcome 2 (abdominal pain≤1 and stool frequency≤3) or Harvey Bradshaw Index<5. Clinical remission in UC is defined as patient-reported outcome 2 (rectal bleeding=0 and stool frequency=0) or Partial Mayo score (<3 and no score>1). Non-corticosteroid-free endoscopic remission is assessed at week 52,^30^ where endoscopic remission in CD is defined as Simple endoscopic score<3 points or absence of ulcerations (eg, SES-CD ulceration subscore=0). Endoscopic remission in UC is defined as Mayo endoscopic score=0 points or UC endoscopic index of severity≤1 point. Disease impact on patient’s life will be assessed by the 32-item version of Inflammatory Bowel Disease Questionnaire (IBDQ) score (number (%) ≤ 170) and the numerical change of the SF36 subscales.

### Other secondary endpoints in the prognostic utility study

The composite secondary outcome is the proportion of patients who experience IBD complications within 52 weeks after inclusion, defined as the cumulative number of patients who experience one of the following (1) need for medication (immunomodulators, biologics or steroids) between diagnosis and 1 year, (2) need for surgery between diagnosis and 1 year, (3) need for hospitalisation between diagnosis and 1 year or (4) relapse between diagnosis and 1 year. Furthermore, the cumulative number of flares, adverse drug reactions, numerical change in the Fatigue Questionnaire, and cumulative glucocorticoid exposure will be assessed. Faecal calprotectin>250 µg/g (no., %), time to start of biological therapy, time to IBD-related surgery or hospitalisation and CD-related surgery (stenosis) will also be measured.

### Mid-term and long-term complications in the prognostic utility study

IBD-related hospitalisations will be assessed and defined as a composite endpoint combining the total number of IBD-related hospitalisations (including readmissions) and the cumulative length of hospital stay. Bowel damage in patients with CD (Lémann index for patients with an MRI), UC-related surgery (colectomy), CD-related surgery (no., %), IBD-related hospitalisations (no., %) and change in disease extent in UC (with a focus on macroscopic proximal disease extent) will be assessed among the mid-term complications. Among the long-term complications, the following three endpoints will be measured: gastrointestinal and extraintestinal dysplasia (no., %), cancer (gastrointestinal and others in no., %) and mortality (no., %).

### Biomarkers

At the time of submission, the NORDTREAT executive committee has approved projects on the following topics in relation to diagnosis and prognosis (including inflammatory intensity, disease extend, tissue damage, tissue repair activity and severe disease course): extracellular matrix proteins, microbiome, mycobiome, faecal markers, genetic risk factors, metabolomics antibodies towards microbial and autoantigens.

### Statistical methods

Referring to earlier studies, approximately 40% of a population referred with suspected IBD will have the diagnosis confirmed according to the ECCO criteria (or comparable).^5 31^ Cost and practical issues will restrict the sample size to approximately 800 patients, with an expected 80% participation rate.

In the *diagnostic test accuracy study*, we will compare two independent binomial proportions, using the likelihood ratio (LR) statistic with a χ^2^ approximation and two-sided significance level (0.05). With an expected sample size of 640 participants (assuming a biomarker positivity-to-negativity ratio of 1 to 1), we will reach an approximate statistical power of 100%, assuming that the proportion of patients diagnosed with IBD is 80% in the biomarker positive group and 20% in the biomarker negative group. If we include 640 study participants, we will potentially (‘rule of thumb’) be able to build a multivariable statistical model with as many as 64 covariates. Thus, we will examine a variety of biochemical variables for diagnosing IBD (see Biomarkers section). The expectation is that a proportion of 100–200 preliminary biomarkers will be evaluated in this model to distinguish non-diagnostic markers and preliminary biomarkers that can be replicated. When applying a significance level of 0.05, each biomarker has a 5% risk of being replicated by chance. Thus, in the evaluation of, for example, 100–200 biomarkers, five to 10 biomarkers may be replicated by chance. In contrast, the risk of not replicating ‘true’ biomarkers with low effects is estimated to be approximately 20%. All replicated biomarkers will be built into a prediction model that will be optimised and evaluated by cross-validation. The primary hypothesis is that the biomarker signature will be able to characterise the participant population into an IBD and a non-IBD group.

In the *prognostic utility study*, we expect a sample size of 256 IBD patients and a 10% event rate for severe IBD within 52 weeks.^32 33^ If we assume a 15% event rate for the biomarker positive group and a 5% event rate for the biomarker negative group, and anticipate an even 1:1 biomarker positive-to-negative distribution, approximately 80 patients in each group will increase the statistical power above the 90% threshold.

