### Prognostic factor research (the prognostic utility study)

The primary statistical analysis will be based on the proportion of participants experiencing severe IBD among biomarker-positive versus biomarker-negative patients. The efficacy of the prognostic biomarker(s) will be considered as the proportion of the patients with different disease outcomes among the biomarker-positive patients compared with the biomarker-negative patients. The associations of the suspected important molecular biomarkers with other variables will be tested with non-parametric tests: with Spearman’s rank correlation (rs) for continuous variables and the Wilcoxon rank-sum test or Kruskal-Wallis test, including a Wilcoxon-type test for trend across ordered groups where appropriate, for categorical variables.

Logistic regression models will be utilised with individual markers as the exposure variables and composite clinical severity as the outcome (dependent variable). The analyses will be adjusted simultaneously for sex, age and prescribed therapy. Potential interactions between biomarker status (positive/negative) and specific drug type will be evaluated too. Covariates comprise of various measures within genetics, transcriptomics, microbiomes and proteomics (see Biomarkers section). We will attempt to develop prediction models containing several conventional risk factors (ie, age, sex and type of drug therapy) with or without any novel biomarkers and calculate improvements in predictive ability using risk discrimination and reclassification measures. We will use a two-stage approach that allows for the examination of centre heterogeneity through the calculation of the C-index, a measure of risk discrimination and changes within each centre before pooling results.

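### The allowance of 64 covariates divides all 640 participants by 10; counted on the 256 expected IBD cases, the same rule supports about 25 parameters

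*Protocol article*

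**What the plan says.** The Statistical methods section starts from a fixed recruitment: "Cost and practical issues will restrict the sample size to approximately 800 patients, with an expected 80% participation rate". It also expects that "approximately 40% of a population referred with suspected IBD will have the diagnosis confirmed". The diagnostic calculation opens "With an expected sample size of 640 participants". The capacity statement comes after it: for that number of participants, and on a rule of thumb, the authors expect to "be able to build a multivariable statistical model with as many as 64 covariates". The next sentence takes that capacity as the reason for examining a range of biochemical variables.

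The outcome of the diagnostic model has two classes. The Primary endpoint(s) section defines it as "IBD (including CD, UC, IBD-U) or non-IBD (patients not diagnosed with IBD) at referral".

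For the prognostic study, Statistical methods expects 256 IBD patients and a 10% rate of severe IBD within 52 weeks. It gives no covariate allowance there. The section on prognostic factor research plans logistic models with individual markers as exposures: "The analyses will be adjusted simultaneously for sex, age and prescribed therapy". Possible interactions between biomarker status and drug type are to be evaluated as well.

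**The concern.** In a logistic model the information about the coefficients is limited by the rarer outcome, so rules of the 10-per-variable kind are counted on the smaller class. Counting them on total enrolment treats the binary outcome as if it were continuous. The stated capacity then comes out too large, by a factor that depends on the prevalence.

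The figure serves as a premise for how many biochemical variables to study, and a later analysis plan could carry it over as an agreed limit. An unpenalised model built up to that limit would be overfitted: its predicted risks would be too extreme, and its apparent discrimination would be better than new patients would show.

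**Working it through.** **Inputs** (Statistical methods unless noted)

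- Recruitment 800, participation 80%.
- Proportion with IBD confirmed: 40%.
- Diagnostic power scenario: IBD in 80% of biomarker-positive and 20% of biomarker-negative participants, in a 1:1 ratio.
- Prognostic study: 256 IBD patients, 10% event rate.
- Outcome IBD or non-IBD (Primary endpoint(s)).
- The divisor of 10 is not written in the article. It is inferred from 640/64.

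**Reproducing the plan's figure**

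- Participants: 800 × 0.80 = 640.
- Covariates: 640 / 10 = 64, an exact match on total enrolment.

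**The same rule on the smaller class**

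- IBD cases: 640 × 0.40 = 256. Non-IBD: 640 − 256 = 384. The smaller class is the 256 cases.
- Supportable parameters: 256 / 10 = 25.6, about 25.
- Overstatement: 64 / 25.6 = 2.5-fold.
- Cases per covariate if 64 were fitted: 256 / 64 = 4.

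**If prevalence is 50% instead**

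- The power scenario implies 0.5 × 0.80 + 0.5 × 0.20 = 0.50, so 640 × 0.50 = 320 cases.
- Supportable parameters: 320 / 10 = 32. Overstatement: 64 / 32 = 2-fold.

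**Prognostic logistic models**

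- Expected events: 256 × 0.10 = 25.6, about 26.
- Supportable parameters: 25.6 / 10 = 2.56, so 2 to 3.
- Planned minimum: marker + sex + age + therapy = 4 terms, even if therapy takes a single coefficient. Interactions come on top.

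**Sensitivity to the divisor**

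| Per variable | Diagnostic, 256 cases | Diagnostic, 320 cases | Prognostic, 25.6 events |
|---|---|---|---|
| 5 | 51.2 | 64.0 | 5.1 |
| 10 | 25.6 | 32.0 | 2.6 |
| 15 | 17.1 | 21.3 | 1.7 |
| 20 | 12.8 | 16.0 | 1.3 |

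**Illustration of what is at stake.** This is a simulation of unpenalised logistic regression with 640 participants, 40% IBD and an assumed true AUC of 0.75, evaluated in 20,000 new patients. The AUC is not a figure from the article.

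- With 64 covariates, repeated runs gave a calibration slope of 0.54 to 0.56, with an apparent AUC of 0.80 to 0.81 against 0.70 in new patients.
- With 25 covariates, the slope was 0.77 to 0.79, with an AUC of 0.77 against 0.73.

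These figures describe a model with every term forced in. That is not the prediction method the article names.

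**The case against.** The strongest reply is that little depends on the number. The article hedges it as a rule of thumb and a maximum. The sample size comes from cost and practicality, and no specified model has 64 terms. The prediction model is to be evaluated by cross-validation, and the closing paragraph of the section on prognostic factor research names LASSO, sparse PLS and tree-based methods. An elaborated analysis plan is also promised before any analysis. All of this stands. It limits the harm and rules out calling the point critical, but it does not make 64 the right reading of the rule.

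Two further replies concern the rule itself. The divisor is inferred, and 64 would also follow from 5 per variable with 320 cases. But the sentence ties 64 to 640 participants, and the stated expectation is 40% IBD, not 50%. The rule is also only a heuristic: in the simulation even 25 unpenalised covariates leave noticeable shrinkage. That is a reason to treat 25 as a rough ceiling; it does not support 64.

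A reader might infer three stronger points that the article does not support.

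- *That 100–200 biomarkers are entered together, beyond even 64.* The wording is loose. However, the text goes on to a 5% error risk for each biomarker and a prediction model made from the replicated ones. That reads as marker-by-marker screening followed by a smaller model.
- *That the planned prediction models will be as overfitted as the 64-covariate simulation.* They are to be regularised and cross-validated, so the simulation does not describe them.
- *That the main prognostic analysis fails.* That analysis compares proportions between biomarker-positive and biomarker-negative patients, and the covariate rule does not touch it. Nor does the article claim 64 covariates for the prognostic study. A particular penalty for the adjusted logistic models would be a matter of preference.

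**Conclusion.** The capacity of 64 covariates is wrong as written. On the article's own prevalence the rule it invokes supports about 25 parameters in an unpenalised diagnostic model, a 2.5-fold overstatement. On the prevalence implied by the power scenario it supports 32, a 2-fold overstatement. The conclusion rests on the inferred divisor of 10 and on the convention of counting the smaller outcome class. With 256 cases, none of the divisors from 5 to 20 yields 64.

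The prognostic part is a secondary note. About 26 events support 2 to 3 parameters, against at least four simultaneous terms before any interaction. At 5 per variable the four main terms would fit, with almost nothing left for interactions.

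This should be fixed, but it does not threaten the sample size, the single-marker accuracy measures or the primary prognostic comparison.

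**What to change.** In Statistical methods, replace 64 with about 25, and show the basis (256 IBD cases / 10). Add that any multivariable model with more candidate terms than this will be fitted only with the regularised methods already named in the section on prognostic factor research.

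In that same section, state that about 26 events are expected, so the rule supports 2 to 3 parameters, and label the biomarker-by-drug interactions exploratory.

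The cost is one corrected number and a few sentences, which can go into the analysis plan promised before any analysis begins. No patients, samples or visits change.
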